**Utrecht, the Netherlands**

#### **Rationale**

#### Although no consensus exists, evidence is accumulating that early treatment with highly active antiretroviral therapy (HAART) in patients who present with an acute or primary HIV infection (PHI) has a beneficial effect on early and late disease progression1-3. In early HIV infection, treatment with HAART may improve the initial cellular response and protect naïve CD4+ cells against infection and thus enhance the immune response4-6. A treatment period during PHI could lower the viral ‘set-point’, characteristic of chronic HIV infection. A lower viral set-point during chronic HIV-infection in its turn is correlated with a better long term clinical outcome. However, the benefits of therapy during PHI have never been demonstrated in clinical trials so far. The optimal duration of such a treatment period during PHI also remains unknown. The lack of evidence regarding the optimal strategy during PHI warrants randomised, controlled investigation. Moreover, the decision whether or not to treat PHI should preferably be placed within the setting of a clinical trial.

#### The aim of this study is to provide data on the effect of treatment during PHI on the viral set-point and the optimal duration of such treatment.

Design

This will be an open-label, semi-factorial, randomized, triple-arm study comparing no treatment versus the use of a quadruple HAART regimen during 6 versus 15 months in patients with a primary HIV-1 infection

The study will enrol patients from physicians who participate in the Dutch HIV Monitoring Foundation (Stichting HIV Monitoring (SHM), formerly known as Athena). The aim of the study is to enrol all patients who meet the inclusion criteria, thus the number of patients is not predetermined. An estimated number of 30 patients will be expected to enrol annually.

### Data from patients who meet the inclusion criteria but refuse therapy will be collected in the same way as data collected from patients on treatment. In this way, these patients form a second reference group of untreated patients. Enrolled patients who discontinue HAART before completing the period of 6 or 15 months will remain in the study and they will be sampled in the same fashion as the other patients.

For patients that need to start therapy, randomization will be limited to the two treatment groups exclusively.

(See flowchart on next page)

###

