**Primary objectives**

To evaluate the effect of 6 or 15 months of treatment with a quadruple combination of HAART versus no treatment in PHI. Efficacy will be evaluated by:

1. the viral set-point reached for the three groups and viral rebound kinetics after treatment discontinuation for the two treatment groups.
2. the time that patients can remain off therapy after treatment discontinuation.

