**Follow up and measurements**

## Screening for adverse effects, physical examination, including vital signs*

### Quality of life assessments by questionnaire

Laboratory tests for safety:

- Hematology, including full blood count (FBC) and leukocyte differentiation*
- Chemistry including liver function test (LFT)*
- Urine analysis, including 24-hrs sample**
- Dual-energy X-ray absorptiometry (DEXA)**
- Markers of bone metabolism, incl. parathyroid hormone**
- Fasting plasma lipids, incl. hs-CRP, apoA1, apoB, insuline**

Virology:

- HIV-1 RNA load in plasma*
- Western blot (baseline)*
- Genotypic resistance at screening*

Immunology:

- T-cell subsets: absolute numbers of CD4/CD3 and CD8/CD3 positive cells (T lymphocytes), the CD4/CD8 ratio*
- Storage of PBMC’s, plasma and serum to perform additional assays
- HLA typing*

*) is part of routine patient care

**) AMC routine patient care

Sampling is to be performed at every patient visit (week , 2, 4, 8, 12, etc.). After treatment discontinuation: at week , 4, 8, 12, 24 and 36. For the no treatment and 6 month treatment groups, visits will be scheduled every 3 months until study completion at week 96 and every three months there after until patients (re)start HAART for chronic HIV infection.

Body material will be stored of all patients who provide appropriate informed consent, with the purpose to do additional investigations after the study has been completed. After the completion of the study, this material will be kept until these investigations have been done, with a maximum of five years. After a maximum duration of five years, these stored materials will be destroyed.

Analysis of the results

Analysis will include a comparison of the three arms (stratified for the patient subgroups A, B and C, see below) for the endpoints listed below. Analysis of the primary endpoint is scheduled for April 2012 based on two more years of enrollment and two years of follow-up after inclusion of the last patient.

Patients will be stratified in three subgroups, according to HIV-1 serology on first day of treatment:

Subgroup A: ELISA: HIV-1 specific antibodies negative.

Subgroup B: ELISA: low level antibodies or HIV-1 specific antibodies positive;

and a negative, incomplete or indeterminate Western Blot (antibodies against a maximum of three of the HIV specific proteins);

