Subgroup C: ELISA: HIV-1 specific antibodies positive and positive Western Blot, but with documented negative HIV-1 ELISA in the preceding 180 days (patient subgroup C).

Primary endpoints:

1. Indication reached for start / reinitiation antiretroviral treatment:
   1. two times a CD4+  T cell count below 350 cells/μl during untreated follow-up
   2. the occurrence of an AIDS defining event
   3. symptomatic chronic HIV infection with severe constitutional symptoms
2. Time between diagnosis and start/reinitiation of HAART
3. Time between treatment discontinuation and reinitiation of HAART
4. Magnitude of viral set-point will be evaluated for both treatment groups 36 weeks after treatment discontinuation, and a comparison will be made between all groups at week 96 (= study end)

Secondary endpoints:

- CD4+ cell counts
- Comparison between all three groups of viral kinetics (including rebound) during the off-treatment periods
- Safety: (serious) adverse events, HIV related events and death
- Quality of life

In selected groups/individuals:

- HIV-1 specific CD4+ and CD8+ T-cell response and their state of activation and maturation
- Humoral immune response parameters

Visit schedule 6 month treatment group

| TRIAL PERIOD | Screening | Baseline |  |  |  |  | Interrupt |  |  |  |  |  |  |  |  |  |
| --- | --- | --- | --- | --- | --- | --- | --- | --- | --- | --- | --- | --- | --- | --- | --- | --- |
| WEEK | -4 TO –1 | 0 | 2 | 4 | 8 | 12 | 24 | 4 | 8 | 12 | 24 | 36 | 48 | 60 | 72 | Etc. †† |
| Study duration (months) |  | 0 |  | 1 | 2 | 3 | 6 | 7 | 8 | 9 | 12 | 15 | 18 | 21 | 24 |  |
| Visit number | 1 | 2 | 3 | 4 | 5 | 6 | 7 | 1a | 2a | 3a | 4a | 5a | 6a | 7a | 8a |  |
| Eligibility criteria | X |  |  |  |  |  |  |  |  |  |  |  |  |  |  |  |
| Informed consent | X |  |  |  |  |  |  |  |  |  |  |  |  |  |  |  |
| Complete medical history | X |  |  |  |  |  |  |  |  |  |  |  |  |  |  |  |
| Prior antiretroviral therapy | X |  |  |  |  |  |  |  |  |  |  |  |  |  |  |  |
| Concomitant medications | X | X | X | X | X | X | X | X | X | X | X | X | X | X | X | X |
| Physical examination | X | X | X | X | X | X | X | X | X | X | X | X | X | X | X | X |
| Routine laboratory testing** | X | X | X | X | X | X | X | X | X | X | X | X | X | X | X | X |
| CD4+ / CD8+ lymphocytes | X | X | X | X | X | X | X | X | X | X | X | X | X | X | X | X |
| ELISA for HIV-1 antibody† | X |  |  |  |  |  |  |  |  |  |  |  |  |  |  |  |

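### Patients who need therapy can be randomised only to 6 or 15 months, yet the planned three-arm comparison is stratified by serology alone, so contrasts with no treatment are not fully randomised

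*Protocol*

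**What the plan says.** The protocol's Design section describes an "open-label, semi-factorial, randomized, triple-arm study comparing no treatment versus the use of a quadruple HAART regimen during 6 versus 15 months". It then sets up a second route into the trial: "For patients that need to start therapy, randomization will be limited to the two treatment groups exclusively". There are therefore two randomisation schemes, a three-way one (none, 6 or 15 months) and a two-way one (6 or 15 months).

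The first sentence under Primary objectives is "To evaluate the effect of 6 or 15 months of treatment with a quadruple combination of HAART versus no treatment in PHI", so treatment against no treatment is a primary contrast.

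Under Analysis of the results the plan is: "Analysis will include a comparison of the three arms (stratified for the patient subgroups A, B and C, see below) for the endpoints listed below". The stratification factor is defined there too: "Patients will be stratified in three subgroups, according to HIV-1 serology on first day of treatment". Under Primary endpoints, the set-point entry adds that "a comparison will be made between all groups at week 96 (= study end").

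Nothing in the protocol limits a comparison with the no-treatment arm to patients who could have been allocated to it, and no stratum identifies the randomisation scheme.

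**The concern.** Randomisation protects a comparison only among patients who could have been allocated to either side of it. Two-way patients could never be allocated to no treatment, so including them puts a selected group on the treated side with nothing to balance it on the other. They are selected because they need therapy, and the first primary endpoint is reaching an indication for therapy, so the selection may well be related to outcome.

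The protocol justifies the trial by the absence of trial evidence on treating primary infection. That contrast is the one that loses part of its protection. A real benefit could be masked, or a difference could appear that only reflects who entered by which route.

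**Working it through.** The protocol gives no sample size, effect size or standard deviation for this contrast, so there is no stated figure to reproduce. The check has four parts.

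**1. Which primary endpoints are exposed**

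| Primary endpoint | Includes the no-treatment arm? | Exposed? |
| --- | --- | --- |
| Indication reached for start or reinitiation | Yes | Yes |
| Time from diagnosis to start or reinitiation | Yes | Yes |
| Time from discontinuation to reinitiation | No, treated arms only | No |
| Set-point 36 weeks after discontinuation | No, treated arms only | No |
| Set-point at week 96, all groups | Yes | Yes |

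**2. Share of two-way patients in each arm**

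Let f be the share of all randomised patients who enter through the two-way scheme. Assume allocation 1:1 in that scheme and 1:1:1 in the other; the protocol gives no ratios.

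- Each treated arm, as a fraction of all patients: f/2 + (1−f)/3 = (2+f)/6.
- No-treatment arm: (1−f)/3.
- Two-way share of each treated arm: (f/2) ÷ ((2+f)/6) = 3f/(2+f).
- Two-way share of the no-treatment arm: 0.

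**3. Bias in the week-96 set-point**

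If two-way patients differ by d log10 for reasons other than treatment, the treated-minus-untreated difference is shifted by d × 3f/(2+f). Both f and d are assumptions.

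| f | Share of each treated arm | Bias, d=0.3 | Bias, d=0.5 | Bias, d=0.8 |
| --- | --- | --- | --- | --- |
| 10% | 0.30/2.10 = 14% | 0.04 | 0.07 | 0.11 |
| 20% | 0.60/2.20 = 27% | 0.08 | 0.14 | 0.22 |
| 35% | 1.05/2.35 = 45% | 0.13 | 0.22 | 0.36 |
| 50% | 1.50/2.50 = 60% | 0.18 | 0.30 | 0.48 |

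Stratifying by A, B and C does not remove this. Within each subgroup the two-way patients still have zero probability of no treatment, so no randomised untreated patient exists with whom to compare them.

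**4. Effect of restricting the contrast**

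With three-way patients only, the two-way share is 0 in every arm and the bias from this source is 0 for any f and d. The price is precision. With equal variances and total N, for combined treated versus none:

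- All patients: variance ∝ 3/(2+f) + 3/(1−f) = 9/[(2+f)(1−f)].
- Three-way only: variance ∝ 3/[2(1−f)] + 3/(1−f) = 9/[2(1−f)].
- Ratio of standard errors: √(1 + f/2), which is √1.10 = 1.05 at f=20% and √1.25 = 1.12 at f=50%.

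For one treated arm versus none, the same algebra gives √[(4+2f)/(4−f)]: √(4.4/3.8) = 1.08 at f=20% and √(5/3.5) = 1.20 at f=50%.

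**The case against.** The best objection is that the protocol never says the two groups are pooled. It says the analysis will include a three-arm comparison, which is not an exhaustive description, and analysis populations are commonly left to a statistical analysis plan. The design is also labelled semi-factorial, which suggests that the authors knew the randomisation was incomplete, and a flowchart that is not available here follows directly after the two-way rule. It stands that pooling is a reading and not a stated word. But the protocol is not silent: it names the comparison and a single stratification factor, and asks for all groups to be compared at week 96. A later plan that followed this text would inherit the problem. The semi-factorial label is not explained or carried into the analysis text, and an allocation diagram would not alter that text.

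Three stronger readings are tempting and are not supported.

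- A reader might infer that the treated arms are known to be sicker. The protocol neither defines need for therapy nor gives a prognosis for these patients, so the direction is a plausible inference only.
- A reader might infer that all primary endpoints are affected. Time from discontinuation to reinitiation and the 36-week set-point involve the treated arms only, and those arms are randomised against each other in both schemes.
- A reader might infer that patients who refuse therapy contaminate the untreated arm. The Design section already sets them apart ("these patients form a second reference group of untreated patients") and nowhere plans to merge them with the randomised arm.

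It is also fair that the magnitude is illustrative. The range spans roughly a factor of ten, and its low end is negligible.

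**Conclusion.** The point holds for comparisons that include the no-treatment arm, and only for those. Followed as written, the plan does not protect them by randomisation, and the serology strata cannot repair this. The imbalance in composition is certain for any f above zero. The size of the resulting bias is not known: 0.04 to 0.48 log10 in week-96 set-point rests on equal allocation, f between 10% and 50%, and d between 0.3 and 0.8 log10, none of which the protocol supplies. If two-way patients have a worse prognosis, the bias runs against treatment. The 6 versus 15 month comparisons stand. Because a primary contrast is affected and analysis wording alone can restore it, the text should be corrected before the analysis.

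**What to change.** Under Analysis of the results, state two things.

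- Every comparison with the no-treatment arm, primary or secondary, uses only patients randomised among all three arms.
- All randomised patients are used for 6 versus 15 months, stratified by randomisation scheme (three-way or two-way) as well as by serology. Stratifying by scheme also covers the case in which the allocation ratio differs between the schemes.

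This changes analysis wording only, provided that each patient's scheme is on record. The cost is some precision in treated versus none: the standard error rises by about 5% at f=20% and 12% at f=50% for the combined treated arms, and by about 8% and 20% for a single treated arm. At the expected 30 patients a year over the two further years of enrolment (60 patients), the contrast would lose 0.2 × 60 = 12 patients at f=20% and 0.5 × 60 = 30 at f=50%, all from the treated side. The result would also apply only to patients for whom no treatment was an open option, which is the only group in which the trial randomises that question.

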**Primary objectives**

To evaluate the effect of 6 or 15 months of treatment with a quadruple combination of HAART versus no treatment in PHI. Efficacy will be evaluated by:

1. the viral set-point reached for the three groups and viral rebound kinetics after treatment discontinuation for the two treatment groups.
2. the time that patients can remain off therapy after treatment discontinuation.

**Secondary objectives**

To evaluate:

1. the effect of treatment on plasma viral load and CD4+ T cells
2. the effect of no treatment versus a treatment duration of 6 versus 15 months on the kinetics of HIV-1 specific CD4+ and CD8+ T-cell responses and their state of maturation, activation and proliferative capacity.
3. the development and efficacy of the humoral immune response.
4. the quality of life.

Inclusion criteria

1. Diagnosis of acute/ recent HIV-1 infection: plasma HIV-1 RNA load detectable and/or detectable serum p24 antigen *and* one of the following:

A ELISA: HIV-1 specific antibodies negative, *or*

B ELISA: low level antibodies or HIV-1 specific antibodies positive

and a negative, incomplete or indeterminate Western Blot (antibodies against a maximum of three of the HIV specific proteins), *or*

C ELISA: HIV-1 specific antibodies positive and positive Western Blot, but with documented negative HIV-1 ELISA in the preceding 180 days.

N.B. Patients should preferably start treatment as soon as possible after diagnosis of acute/ recent HIV-1 infection, but in any case within 180 days after diagnosis.

1. Written informed consent, including permission to store samples.
2. Patient is at least 18 years of age.
3. For female subjects: the use of adequate contraception

**Exclusion criteria**

1. Previous test result with HIV-1 RNA detectable or P24 antigen positive > 180 days before presentation
2. For female subjects: pregnancy (positive urine pregnancy test) or breast feeding

###### Study drugs and dosages

Subjects randomized to treatment will receive 6 or 15 months of the following regimen:

- emtricitabine/tenofovir (Truvada) 200/245 mg once daily
- efavirenz (Stocrin)* 600 mg once daily
- lopinavir/ritonavir (Kaletra) 600/150 mg b.i.d

N.B. After one measurement of HIV-RNA load < 50 copies/ml, Kaletra is to be discontinued.

**Follow up and measurements**

## Screening for adverse effects, physical examination, including vital signs*

### Quality of life assessments by questionnaire

Laboratory tests for safety:

- Hematology, including full blood count (FBC) and leukocyte differentiation*
- Chemistry including liver function test (LFT)*
- Urine analysis, including 24-hrs sample**
- Dual-energy X-ray absorptiometry (DEXA)**
- Markers of bone metabolism, incl. parathyroid hormone**
- Fasting plasma lipids, incl. hs-CRP, apoA1, apoB, insuline**

Virology:

- HIV-1 RNA load in plasma*
- Western blot (baseline)*
- Genotypic resistance at screening*

Immunology:

- T-cell subsets: absolute numbers of CD4/CD3 and CD8/CD3 positive cells (T lymphocytes), the CD4/CD8 ratio*
- Storage of PBMC’s, plasma and serum to perform additional assays
- HLA typing*

*) is part of routine patient care

**) AMC routine patient care

Sampling is to be performed at every patient visit (week , 2, 4, 8, 12, etc.). After treatment discontinuation: at week , 4, 8, 12, 24 and 36. For the no treatment and 6 month treatment groups, visits will be scheduled every 3 months until study completion at week 96 and every three months there after until patients (re)start HAART for chronic HIV infection.

Body material will be stored of all patients who provide appropriate informed consent, with the purpose to do additional investigations after the study has been completed. After the completion of the study, this material will be kept until these investigations have been done, with a maximum of five years. After a maximum duration of five years, these stored materials will be destroyed.

Analysis of the results

Analysis will include a comparison of the three arms (stratified for the patient subgroups A, B and C, see below) for the endpoints listed below. Analysis of the primary endpoint is scheduled for April 2012 based on two more years of enrollment and two years of follow-up after inclusion of the last patient.

Patients will be stratified in three subgroups, according to HIV-1 serology on first day of treatment:

Subgroup A: ELISA: HIV-1 specific antibodies negative.

Subgroup B: ELISA: low level antibodies or HIV-1 specific antibodies positive;

and a negative, incomplete or indeterminate Western Blot (antibodies against a maximum of three of the HIV specific proteins);

Subgroup C: ELISA: HIV-1 specific antibodies positive and positive Western Blot, but with documented negative HIV-1 ELISA in the preceding 180 days (patient subgroup C).

Primary endpoints:

1. Indication reached for start / reinitiation antiretroviral treatment:
   1. two times a CD4+  T cell count below 350 cells/μl during untreated follow-up
   2. the occurrence of an AIDS defining event
   3. symptomatic chronic HIV infection with severe constitutional symptoms
2. Time between diagnosis and start/reinitiation of HAART
3. Time between treatment discontinuation and reinitiation of HAART
4. Magnitude of viral set-point will be evaluated for both treatment groups 36 weeks after treatment discontinuation, and a comparison will be made between all groups at week 96 (= study end)

Secondary endpoints:

- CD4+ cell counts
- Comparison between all three groups of viral kinetics (including rebound) during the off-treatment periods
- Safety: (serious) adverse events, HIV related events and death
- Quality of life

In selected groups/individuals:

- HIV-1 specific CD4+ and CD8+ T-cell response and their state of activation and maturation
- Humoral immune response parameters

Visit schedule 6 month treatment group

| TRIAL PERIOD | Screening | Baseline |  |  |  |  | Interrupt |  |  |  |  |  |  |  |  |  |
| --- | --- | --- | --- | --- | --- | --- | --- | --- | --- | --- | --- | --- | --- | --- | --- | --- |
| WEEK | -4 TO –1 | 0 | 2 | 4 | 8 | 12 | 24 | 4 | 8 | 12 | 24 | 36 | 48 | 60 | 72 | Etc. †† |
| Study duration (months) |  | 0 |  | 1 | 2 | 3 | 6 | 7 | 8 | 9 | 12 | 15 | 18 | 21 | 24 |  |
| Visit number | 1 | 2 | 3 | 4 | 5 | 6 | 7 | 1a | 2a | 3a | 4a | 5a | 6a | 7a | 8a |  |
| Eligibility criteria | X |  |  |  |  |  |  |  |  |  |  |  |  |  |  |  |
| Informed consent | X |  |  |  |  |  |  |  |  |  |  |  |  |  |  |  |
| Complete medical history | X |  |  |  |  |  |  |  |  |  |  |  |  |  |  |  |
| Prior antiretroviral therapy | X |  |  |  |  |  |  |  |  |  |  |  |  |  |  |  |
| Concomitant medications | X | X | X | X | X | X | X | X | X | X | X | X | X | X | X | X |
| Physical examination | X | X | X | X | X | X | X | X | X | X | X | X | X | X | X | X |
| Routine laboratory testing** | X | X | X | X | X | X | X | X | X | X | X | X | X | X | X | X |
| CD4+ / CD8+ lymphocytes | X | X | X | X | X | X | X | X | X | X | X | X | X | X | X | X |
| ELISA for HIV-1 antibody† | X |  |  |  |  |  |  |  |  |  |  |  |  |  |  |  |
| Western blot† | X |  |  |  |  |  |  |  |  |  |  |  |  |  |  |  |
| Genotypic resistance | X |  |  |  |  |  |  |  |  |  |  |  |  |  |  |  |
| Plasma HIV-1 RNA levels | X | X | X | X | X | X | X | X | X | X | X | X | X | X | X | X |
| Urine pregnancy test | X | X |  |  |  |  |  |  |  |  |  |  |  |  |  |  |
| Fasting plasma lipid spectrum* | X | X |  | X |  |  | X | X |  |  |  | X |  |  | X |  |
| Urine analysis* |  | X |  |  |  |  | X |  |  |  |  |  |  |  | X |  |
| Markers bone metabolism* |  | X |  |  |  |  | X |  |  |  |  |  |  |  | X |  |
| PBMC virology | X |  |  |  |  |  | X |  |  |  | X |  |  |  |  |  |
| PBMC/plasma/serum storage* |  | X | X | X | X | X | X | X | X | X |  | X | X | X | X | X |
| DEXA* |  | X |  |  |  |  |  |  |  |  |  |  |  |  | X |  |
| Quality of life questionnaire | X | X |  |  | X |  | X |  | X |  | X | X | X | X | X |  |
| Volume of blood drawn (ml) | 76 | 72 | 72 | 72 | 72 | 72 | 72 | 72 | 72 | 72 | 72 | 72 | 72 | 72 | 72 | 72 |

*) AMC only

**) hematology, including full blood count, leukocytes + differentiation, clinical chemistry, including liver enzymes

†) repeated until positive/complete/stable

††) suggested regular healthcare visits every three months

Visit schedule 15 month treatment group

| TRIAL PERIOD | Screening | Baseline |  |  |  |  |  |  |  | Interrupt |  |  |  |  |  |  |
| --- | --- | --- | --- | --- | --- | --- | --- | --- | --- | --- | --- | --- | --- | --- | --- | --- |
| WEEK | -4 TO –1 | 0 | 2 | 4 | 8 | 12 | 24 | 36 | 48 | 60 | 4 | 8 | 12 | 24 | 36 | Etc. †† |
| Study duration (months) |  | 0 |  | 1 | 2 | 3 | 6 | 9 | 12 | 15 | 16 | 17 | 18 | 21 | 24 |  |
| Visit number | 1 | 2 | 3 | 4 | 5 | 6 | 7 | 8 | 9 | 10 | 1a | 2a | 3a | 4a | 5a |  |
| Eligibility criteria | X |  |  |  |  |  |  |  |  |  |  |  |  |  |  |  |
| Informed consent | X |  |  |  |  |  |  |  |  |  |  |  |  |  |  |  |
| Complete medical history | X |  |  |  |  |  |  |  |  |  |  |  |  |  |  |  |
| Prior antiretroviral therapy | X |  |  |  |  |  |  |  |  |  |  |  |  |  |  |  |
| Concomitant medications | X | X | X | X | X | X | X | X | X | X | X | X | X | X | X | X |
| Physical examination | X | X | X | X | X | X | X | X | X | X | X | X | X | X | X | X |
| Routine laboratory testing** | X | X | X | X | X | X | X | X | X | X | X | X | X | X | X | X |
| CD4+ / CD8+ lymphocytes | X | X | X | X | X | X | X | X | X | X | X | X | X | X | X | X |
| ELISA for HIV-1 antibody† | X |  |  |  |  |  |  |  |  |  |  |  |  |  |  |  |
| Western blot† | X |  |  |  |  |  |  |  |  |  |  |  |  |  |  |  |
| Genotypic resistance | X |  |  |  |  |  |  |  |  |  |  |  |  |  |  |  |
| Plasma HIV-1 RNA levels | X | X | X | X | X | X | X | X | X | X | X | X | X | X | X | X |
| Urine pregnancy test | X | X |  |  |  |  |  |  |  |  |  |  |  |  |  |  |
| Fasting plasma lipid spectrum* | X | X |  | X |  |  | X |  |  | X | X |  |  |  | X |  |
| Urine analysis* |  | X |  |  |  |  |  |  |  | X |  |  |  |  | X |  |
| Markers bone metabolism* |  | X |  |  |  |  |  |  |  | X |  |  |  |  | X |  |
| PBMC virology* | X |  |  |  |  |  | X |  | X |  |  |  |  | X |  |  |
| PBMC/plasma/serum storage* |  | X | X | X | X | X |  | X |  | X | X | X | X |  | X | X |
| DEXA* |  | X |  |  |  |  |  |  |  | X |  |  |  |  | X |  |
| Quality of life questionnaire | X | X |  |  | X |  | X | X | X | X |  | X | X | X | X |  |
| Volume of blood drawn (ml) | 76 | 72 | 72 | 72 | 72 | 72 | 72 | 72 | 72 | 72 | 72 | 72 | 72 | 72 | 72 | 72 |

*) AMC only

**) hematology, including full blood count, leukocytes + differentiation, clinical chemistry, including liver enzymes

†) repeated until positive/complete/stable

††) suggested regular healthcare visits every three months

Visit schedule no treatment group

| TRIAL PERIOD | Screening | Baseline |  |  |  |  |  |  |  |  |  |  |  |  |
| --- | --- | --- | --- | --- | --- | --- | --- | --- | --- | --- | --- | --- | --- | --- |
| WEEK | -4 TO –1 | 0 | 2 | 4 | 8 | 12 | 24 | 36 | 48 | 60 | 72 | 84 | 96 | Etc. †† |
| Study duration (months) |  | 0 |  | 1 | 2 | 3 | 6 | 9 | 12 | 15 | 18 | 21 | 24 |  |
| Visit number | 1 | 2 | 3 | 4 | 5 | 6 | 7 | 8 | 9 | 10 | 11 | 12 | 13 |  |
| Eligibility criteria | X |  |  |  |  |  |  |  |  |  |  |  |  |  |
| Informed consent | X |  |  |  |  |  |  |  |  |  |  |  |  |  |
| Complete medical history | X |  |  |  |  |  |  |  |  |  |  |  |  |  |
| Prior antiretroviral therapy | X |  |  |  |  |  |  |  |  |  |  |  |  |  |
| Concomitant medications | X | X | X | X | X | X | X | X | X | X | X | X | X | X |
| Physical examination | X | X | X | X | X | X | X | X | X | X | X | X | X | X |
| Routine laboratory testing** | X | X | X | X | X | X | X | X | X | X | X | X | X | X |
| CD4+ / CD8+ lymphocytes | X | X | X | X | X | X | X | X | X | X | X | X | X | X |
| ELISA for HIV-1 antibody† | X | X | X | X | X | X | X | X | X | X | X | X | X | X |
| Western blot† | X | X |  | X | X | X | X |  |  |  |  |  |  |  |
| Genotypic resistance | X |  |  |  |  |  |  |  |  |  |  |  |  |  |
| Plasma HIV-1 RNA levels | X | X | X | X | X | X | X | X | X | X | X | X | X | X |
| Urine pregnancy test | X | X |  |  |  |  |  |  |  |  |  |  |  |  |
| Fasting plasma lipid spectrum* | X | X |  |  |  |  | X | X |  |  |  |  | X |  |
| Urine analysis* |  | X |  |  |  |  |  | X |  |  |  |  | X |  |
| Markers bone metabolism* |  | X |  |  |  |  |  | X |  |  |  |  | X |  |
| PBMC direct analysis* | X |  |  |  |  |  | X |  |  |  |  | X |  |  |
| PBMC/plasma/serum storage* |  | X | X | X | X | X |  | X | X | X | X |  | X | X |
| DEXA* |  | X |  |  |  |  |  |  |  |  |  |  | X |  |
| Quality of life questionnaire | X | X |  |  | X |  | X | X | X | X | X | X | X |  |
| Volume of blood drawn (ml) | 76 | 76 | 72 | 76 | 76 | 76 | 76 | 72 | 72 | 72 | 72 | 72 | 72 |  |

*) AMC only

**) hematology, including full blood count, leukocytes + differentiation, clinical chemistry, including liver enzymes

†) repeated until positive/complete/stable

††) suggested regular healthcare visits every three month

